## Abstract

**Background:**

Vital signs are the primary indicator of physiological status and for determining the need for urgent clinical treatment. Yet, if physiological signs of deterioration are missed, misinterpreted or mismanaged, then critical illness, unplanned intensive care admissions, cardiac arrest and death may ensue. Although evidence demonstrates the benefit of early recognition and management of deteriorating patients, failure to escalate care and manage deteriorating patients remains a relatively frequent occurrence in hospitals.

**Methods/design:**

A pragmatic cluster-randomised controlled trial design will be used to measure clinical effectiveness and cost of a facilitation intervention to improve nurses’ vital sign measurement, interpretation, treatment and escalation of care for patients with abnormal vital signs. A cost consequence analysis will evaluate the intervention cost and effectiveness, and a process evaluation will determine how the implementation of the intervention contributes to outcomes. We will compare clinical outcomes and costs from standard implementation of clinical practice guidelines (CPGs) to facilitated implementation of CPGs. The primary outcome will be adherence to the CPGs by nurses, as measured by escalation of care as per organisational policy. The study will be conducted in four Australian major metropolitan teaching hospitals. In each hospital, eight to ten wards will be randomly allocated to intervention and control groups. Control wards will receive standard implementation of CPGs, while intervention wards will receive standard CPG implementation plus facilitation, using facilitation methods and processes tailored to the ward context. The intervention will be administered to all nursing staff at the ward level for 6 months. At each hospital, two types of facilitators will be provided: a hospital-level facilitator as the lead; and two ward-level facilitators for each ward.

**Discussion:**

This study uses an innovative, networked approach to facilitation to enable uptake of CPGs. Findings will inform the intervention utility and knowledge translation measurement approaches. If successful, the study methodology and intervention has potential for translation to other health care standards.

**Trial registration:**

Australian New Zealand Clinical Trials Registry (ANZCTR), ACTRN12616000544471p

## Background

Contemporary hospitals treat increasingly complex patients suffering from multiple health care problems [1]. Although there are many tools available to assess patients’ responses to illness and treatment, vital signs (VS) are the primary indicator of physiological status and the most common assessment technique employed in health care. If physiological signs of deterioration are missed, misinterpreted or mismanaged, then serious adverse events (SAEs) such as critical illness, cardiac arrest, unplanned intensive care admissions and death may result. Identification of abnormal VS can assist in the detection of at-risk patients minutes to hours before the occurrence of SAEs [2]. VS measurement and escalation of care is fundamental to patient safety and the first step in patient rescue.

International evidence highlights the severity of adverse outcomes when VS are not recognised as abnormal or responded to appropriately [3, 4]. An Australian study found that the presence of three or more abnormal VS was associated with a 19-fold increase in mortality risk as compared to patients with a single abnormal VS [5]. Since 1995, Australia has led the way in system redesign, countering the morbidity and mortality associated with failure to rescue. One strategy, rapid response systems (RRS) and in particular medical emergency teams (MET) takes critical care expertise to the wards when predetermined activation criteria (VS and other measurements) are met. The success of MET and impact on patient outcomes depends on activation actually occurring when indicated. However, we have shown that this does not always occur with 3–53% of patients meeting criteria for activation actually receiving a RRS call [6–8]. Failure to call the RRS for patients fulfilling activation criteria occurs despite the release of international guidelines [9, 10] and the prioritisation of Standard 9 (recognition and response to clinical deterioration in acute health care) as one of the ten National Quality and Safety Health Service (NQSHS) Standards required for Australian hospital accreditation from 2011 [11]. A significant gap between current evidence and practice exists.

In our survey of 1688 patients in 10 acute care hospitals, the prevalence of patients fulfilling MET criteria in the 24 h prior to data collection was 5.3% and on the day of observation was 3.3% [7]. Of the 55 patients who fulfilled the MET criteria, only 2 (3.6%) had a MET call activated within 24 h. Patients who fulfilled MET criteria at the time of vital sign acquisition were more likely to die in hospital (RR = 2.95; 95% confidence interval (CI) 1.22 to 7.15) or within 30 days (RR = 2.64; 95% CI 1.37 to 5.11). Our research has also shown the incidence of patients fulfilling MET calling criteria to be 14.4% during their hospital admission, and of those patients, only 2.9% received a MET call. Further, patients who fulfilled MET activation criteria had double the hospital length of stay [8]. Thus, timely and effective intervention is critical.

Although a growing body of international evidence demonstrates the benefit of early recognition and management of deteriorating patients, suboptimal management has serious consequences and represents a research-practice gap [12]. One recent study further highlighted this gap in a sample of 422 patients; escalation was indicated on 109 occasions, yet contrary to hospital policy, only 58 (53%) were escalated appropriately [6]. This failure to escalate and manage patients concurs with our previous research [7] and others internationally [3, 4, 13]. There is a need to understand the causes, mechanisms and strategies to overcome the problem using knowledge translation (KT) frameworks.

One widely researched and used KT framework is *the Promoting Action on Research Implementation in Health Services* (PARIHS) Framework [14–16], which views implementation as a dynamic and multi-faceted process. The proposition is that successful implementation is a function of the nature and type of evidence, the qualities of the context in which the evidence is being introduced, and the way the process is facilitated [15]. Although many strategies are thought to be effective in promoting individual and organisational change, the change agent role is believed to be a key ingredient for KT. Additionally, systematic reviews have found educational outreach of practice facilitation in health care have improved patient care [17, 18].

## Methods/design

This knowledge translation study uses a pragmatic cluster-randomised controlled trial (C-RCT) design, with process evaluation and cost consequence analysis, to measure the clinical effectiveness and costs of a facilitation intervention to improve nurses’ VS measurement, interpretation, treatment and escalation of patients with abnormal VS. We will compare outcomes and costs from standard implementation of clinical practice guidelines (CPGs) to facilitated implementation of CPGs. An embedded process evaluation will assist in obtaining a deeper understanding of the variable contexts of implementation, the barriers and enablers encountered, the response by stakeholders and the resources required for implementation.

This project aims the following:To improve nurses’ adherence to clinical practice guidelines (CPG) for identifying and managing deteriorating patients in hospitalTo determine the clinical effectiveness and costs of a **F**aci**l**itation **I**ntervention for **P**ractice improvement (FLIP) to improve nurses’ adherence to the CPGsTo assess the impact of contextual characteristics on processes and outcomes of implementationTo develop and disseminate recommendations to health policy and practice decision makers

### Primary hypothesis

Nurses in wards receiving standard CPG implementation *plus* a facilitation intervention (FLIP) will demonstrate greater adherence to CPGs for identifying and managing deteriorating patients compared to nurses in wards receiving standard CPG dissemination alone.

### Secondary hypotheses

*Nursing practice outcomes*: Patients in wards receiving the FLIP will have increased documented VS (complete sets), repeated VS within 30 min of obtaining an abnormal VS, documented nursing scope of practice interventions in response to abnormal vital signs, increased activations for urgent clinical reviews and MET calls in patients fulfilling the criteria. *Clinical Outcomes*: Patients in wards receiving the FLIP will have fewer cardio-respiratory arrests, less unplanned intensive care unit (ICU) admissions, lower unexpected hospital mortality rates and reduced hospital length of stay (HLOS). *Health Economic Outcome*: The cost of implementing the FLIP will be offset by savings from shorter HLOS and reduced ICU admissions. FLIP will represent a cost-effective use of resources.

The study is designed to adhere to the Good Clinical Practice (GCP) Guidelines for national ethics standards and is consistent with the C-RCT CONSORT statement [19] and the CHEERS statement [20], ensuring it meets international ethical and scientific quality standards for reporting clinical trials that include an economic evaluation (see Fig. 1).

**Fig. 1 Fig1:**
[figure not shown]
Consort diagram. This figure provides the flow diagram of the phases of the cluster-randomised controlled trial

### Outcome measures

#### Primary outcome

The primary outcome is the adherence to the CPGs for recognition and management of clinical deterioration by nurses, as measured by the escalation of care as per hospital policy.

#### Secondary outcomes

The secondary outcomes are as follows: *Nursing practice*: Nurses’ adherence to CPGs measured by proportions of documented VS (complete set), repeated VS within 30 min of obtaining an abnormal VS and documented nursing scope of practice interventions in response to abnormal vital signs; proportions of activated urgent clinical reviews and MET calls in patients fulfilling the criteria. *Clinical:* Rates of cardio-respiratory arrests, unplanned admissions to ICU, unexpected hospital mortality and mean HLOS. *Costs:* Mean additional cost of implementing the intervention and mean/median total hospital cost and HLOS for patients. *Process evaluation*: measurement of the fidelity of the facilitation intervention, contextual influences and impact on ward processes and practice.

### Setting

Four hospitals in Victoria, Australia, will be the setting for this study. All are acute, major metropolitan teaching hospitals that have more than 400 beds, employ over 1300 nurses and cover both acute and specialist services. Sponsorship for the study was sought from the Executive Directors of Nursing and Chief Executive Officers of each hospital prior to the funding application. Within each hospital, eight to ten wards will be randomly allocated to either intervention or control groups; the intervention will be delivered at ward level. Each ward is considered a cluster for the purpose of analysis. Wards will be eligible for inclusion if they contain 18 or more beds and they receive support from the hospital’s MET. Critical care, emergency, paediatrics, maternity, peri-operative and psychiatric areas will be excluded because they use an alternative response system for patient deterioration.

### Sample/participants

All staff working within study wards and whose role is direct care delivery will be involved in the study. Each ward has a permanent staff, reducing the likelihood of contamination from staff movement. Nurse managers (NM) will recruit staff to participate in focus groups or individual interviews for the process evaluation; the RA will obtain consent. Medical records of patients from participating wards will be audited over three randomly selected 24-h periods during 1 week at three time points (baseline, immediately post-intervention and 6 months post-intervention) to identify all ward patients in a 24-h period who have abnormal VS. These cohorts of patients will be followed up for the duration of their hospital stay and analysed according to ward (intervention or control), irrespective of subsequent ward transfers that may occur using the principles of intention-to-treat (ITT) analysis.

### Sample size

From a medical record review in one of the sites, the rate of adherence to escalation policy after abnormal VS measurement was 53% [6]. Sample size calculations are based on a 50% rate of adherence to escalation as per hospital policy. To detect a 20% improvement in adherence rate in the intervention group immediately following and 6 months post-intervention, 270 documented abnormal VSs per time point per study arm are required. Our sample size has been inflated to allow for a design effect of 1.5, accounting for within-patient autocorrelation and within ward clustering effect. Type I error is set at a 1% significance level accounting for multiple comparisons and study power is set to 90%. For secondary outcomes, we have 80% power to detect an odds ratio of at least 1.8 in post-intervention comparisons for an improved adherence rate in the intervention compared to the control group. For all other secondary outcomes, power calculations have been based on combining immediately following intervention and 6 months post-intervention data. For the unplanned ICU admission rate, a minimum of 0.3% difference (1.2 vs 0.9%); for MET call rate a minimum of 2.3% absolute difference (3 vs 0.7%); and at least 1.6 day (IQR = 20) median absolute difference (12 vs 10.4) for hospital LOS is detectable at 80% power. Due to a low incidence of cardio-respiratory arrests and hospital mortality, a power analysis is based on combining mortality and code blue, resulting in 80% power to detect a minimum 2.3% absolute difference (3 vs 0.7%).

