### Data analysis

Quantitative methods will be used to analyse patient, health services utilization and economic outcomes. Main and secondary outcome analysis will be based on all randomised wards and selected participants (intention-to-treat analysis). To account for within-patient correlation, due to multiple measurements from the same patient during assessment days, we will implement generalized estimating equation (GEE) models with binary outcome and logit link for all rate outcome comparisons [23]. The Cochran-Mantel-Haenszel (CMH) test will be used to compare proportions. Clustering effects for wards will be evaluated by calculating intraclass correlation coefficients and, if necessary, a fixed effect nominal factor will be included in GEEs to account for ward impact. A series of exploratory analyses will be conducted on subgroups and the impact of covariates on estimates of the effect of the intervention. A nonparametric median test will be used for HLOS comparison. In supportive analysis, HLOS will be considered as time to event data. Survival rates will be calculated and illustrated by the Kaplan–Meier method and further analysed by the log-rank test for univariate analysis (stratified by wards). Variables that reveal prognostic or effect modifying potential on the outcome as suggested by univariate analysis will subsequently be evaluated by the proportional Cox regression for multivariate analysis. Hazard ratios with the corresponding 95% confidence intervals will be reported. A *p* value of <0.05 is considered statistically significant. Data will be analysed using Stata version 14 or later [24].

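### The 80% power for an odds ratio of 1.8 names no significance level; it fits the 5% of Data analysis but not the 1% of Sample size, and the two are not reconciled

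*Protocol article*

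**What the plan says.** The Sample size section of the protocol article gives the inputs for the adherence comparison in this order.

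- Control rate: "Sample size calculations are based on a 50% rate of adherence to escalation as per hospital policy".
- Effect: "To detect a 20% improvement in adherence rate in the intervention group immediately following and 6 months post-intervention".
- Number: "270 documented abnormal VSs per time point per study arm are required".
- Inflation: "Our sample size has been inflated to allow for a design effect of 1.5", which covers both repeated measurements within patients and clustering within wards.
- Error rates: "Type I error is set at a 1% significance level accounting for multiple comparisons and study power is set to 90" per cent.

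The next sentence turns to the secondary outcomes and says that "we have 80% power to detect an odds ratio of at least 1.8 in post-intervention comparisons". It gives a new power, 80%, and no significance level. The section then says that the two post-intervention time points are combined for all other secondary outcomes, so combining is not stated for this one.

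The Data analysis section gives one criterion, which it does not limit to any outcome: a p "value of <0.05 is considered statistically significant".

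**The concern.** The 1% level is the only one named in the Sample size section. It is worded generally, and the odds ratio sentence follows it directly. A reader who carries it forward, together with the design effect, does not arrive at 80%. A reader who uses the level from Data analysis does, but then has no place in the analysis where the 1% allowance for multiple comparisons takes effect.

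Two things depend on which level is meant. One is the threshold for the primary result: an adherence comparison with p between 0.01 and 0.05 would be positive under Data analysis and not positive under Sample size. The other is how to read a null result on the secondary adherence outcomes. A study with 80% power for an odds ratio of 1.8 tells the reader more by failing to find it than a study with 57% power.

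**Working it through.** **Inputs.** All are from the Sample size section unless noted.

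- Control adherence p1 = 0.50.
- 270 abnormal vital signs per arm per time point, design effect 1.5, so the effective number is 270 / 1.5 = 180 per arm.
- Levels: 1% (Sample size) and 5% (Data analysis). Sidedness is not stated; two-sided is assumed, so z = 2.576 or 1.960.
- Equal arms, from the 1:1 allocation in Randomisation.

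**Step 1: reproduce the primary sample size.** For 50% versus 70%, 1% two-sided and 90% power, with pooled variance under the null:

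n = [2.576 × √(2 × 0.6 × 0.4) + 1.282 × √(0.25 + 0.21)]² / 0.20² = 177 per arm after rounding up.

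177 × 1.5 = 265.5, within 2% of the stated 270. The primary calculation therefore used the 1% level and the design effect, and read the 20% improvement as an absolute difference.

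**Step 2: the effect in the odds ratio sentence.** With control odds of 1, p2 = 1.8 / 2.8 = 0.643, so the difference is 0.143.

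**Step 3: power at 180 effective per arm.** With unpooled variance:

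SE = √[(0.2500 + 0.2296) / 180] = 0.0516, and 0.1429 / 0.0516 = 2.768.

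- 5%: Φ(2.768 − 1.960) = Φ(0.808) = 79.0%.
- 1%: Φ(2.768 − 2.576) = Φ(0.192) = 57.6%.

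With pooled variance under the null the results are 78.4% and 56.5%.

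**Step 4: all four combinations for an odds ratio of 1.8.**

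| Level (two-sided) | Design effect | Power, unpooled | Power, pooled |
|---|---|---|---|
| 5% | 1.5 | 79.0% | 78.4% |
| 1% | 1.5 | 57.6% | 56.5% |
| 1% | none | 79.2% | 78.4% |
| 5% | none | 92.4% | 92.1% |

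**Step 5: odds ratio detectable with 80% power, design effect 1.5.** At 5% it is 1.81 (unpooled) or 1.82 (pooled), which rounds to the stated 1.8. At 1% it is 2.07 or 2.09. Put as a sample size, an odds ratio of 1.8 at 1% with 80% power needs 279 × 1.5 = about 419 per arm.

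**Step 6: sensitivity at 1% with design effect 1.5.** A Wald test on the log odds ratio gives 56.1%. A one-sided test gives 66.2%. Over all control rates tried, from 5% to 95%, power never exceeds 57.7% (pooled). No such variant brings the 1% level to 80%.

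**Step 7: another secondary figure.** For MET calls, 3% versus 0.7% is said to be detectable with 80% power on combined data. The denominator is not given. Assuming 2 × 270 = 540 per arm and no design effect, power is 80.2% at 5% and 59.1% at 1%. With the design effect (360 effective) it is 63% at 5%. On that assumption the MET figure points to 5%, but without the design effect that the odds ratio figure needs at that level.

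**The case against.** A reader might infer that the 80% is simply wrong, about 22 points too high under the plan's own assumptions. The document does not support that. The odds ratio sentence states no level. It opens a new topic, secondary outcomes, and replaces the 90% power of the sentence before it; if the 90% does not carry forward, the 1% need not either. The 5% level is not imported from outside, since Data analysis states it, and with the stated design effect it gives a detectable odds ratio of 1.81 to 1.82. The MET figure leans the same way, though only with an assumed denominator and no design effect. No arithmetic error is shown.

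The number is also an assumption. 270 is what the plan requires, whereas Sample/participants and Assessments describe reviewing all inpatients of the study wards on the selected days, so more abnormal vital signs may be collected. Some secondary adherence measures, such as complete sets of vital signs, need not be counted per abnormal reading.

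All of this stands, and it makes the 57% a conditional figure. It does not settle which level applies. The 0.05 in Data analysis is not confined to secondary outcomes, so reading it as the answer for them also makes it the threshold for the primary outcome, against the 1% used to size the trial. Nor is this detail that an article would leave to a longer document: both levels are printed, and they conflict.

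**Conclusion.** The point holds as an unreconciled significance level, not as a miscalculated power. With 270 per arm, design effect 1.5, 50% control adherence and a two-sided test, the stated 80% for an odds ratio of 1.8 agrees with a 5% test (78% to 79%). It does not agree with a 1% test (56.5% to 57.6%, with about 2.1 detectable at 80% power). The choice of variance formula accounts for the one-point spread in each range. Dropping the design effect would also give about 79% at 1%, but the section says that the sample size includes it.

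The gap of about 22 points applies only if 1% governs the secondary adherence comparisons, which the document does not say. What is certain is that the 1% level and the 80% figure cannot both govern them, and that the primary comparisons have been given two different thresholds.

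**What to change.** Reconcile the Sample size and Data analysis sections.

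- **Preferred.** State that the primary adherence comparisons are tested at 1% and the secondary adherence outcomes at 5%, name the 5% level and the design effect in the odds ratio sentence, and keep 80% power for an odds ratio of 1.8. In Data analysis, replace the general 0.05 with these two levels.
- **Alternative.** If 1% is meant for the secondary adherence outcomes as well, restate the figure as 80% power for an odds ratio of about 2.1 (about 57% for 1.8), and give 1% for these comparisons in Data analysis.

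In either case say whether the tests are two-sided. The figure should be changed only after checking which level was used: rewriting it to 2.1 would introduce an error if the calculation was done at 5%.

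The cost is wording only; neither the sample nor the data collection changes. The preferred route makes the primary threshold in the analysis section stricter. The alternative does the same and also makes the stated power for the secondary outcomes less favourable.

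### The 80% power claimed for unplanned ICU admission (1.2 vs 0.9%) needs about 18,100 patients per arm; power is about 7% at the only size the section implies, and the length-of-stay figure does not reproduce there either

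*Protocol article*

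**What the plan says.** All the power statements are in the Sample size section of the protocol article.

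- Primary outcome: "270 documented abnormal VSs per time point per study arm are required". This includes a design effect of 1.5, and "Type I error is set at a 1% significance level accounting for multiple comparisons and study power is set to 90"%.
- Secondary outcomes other than adherence: "power calculations have been based on combining immediately following intervention and 6 months post-intervention data".
- On that pooled basis the section lists "For the unplanned ICU admission rate, a minimum of 0.3% difference (1.2 vs 0.9"%), then "for MET call rate a minimum of 2.3% absolute difference (3 vs 0.7"%), then "at least 1.6 day (IQR = 20) median absolute difference (12 vs 10.4) for hospital LOS is detectable at 80% power".
- For mortality combined with code blue it gives a calculation "resulting in 80% power to detect a minimum 2.3% absolute difference (3 vs 0.7"%).

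No patient count is given for any of these secondary figures. Under Sample/participants, the patients followed to discharge are those found to have abnormal vital signs on three audit days at each time point. Under Data analysis, length of stay is compared with a median test, and a *p* "value of <0.05 is considered statistically significant".

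**The concern.** The pooled-data figures share one basis, yet the minimum detectable difference is 0.3 points for ICU admission and 2.3 points for MET calls. The ICU rates are somewhat lower than the MET rates, but not by enough to make a difference nearly eight times smaller (2.3/0.3 = 7.7) detectable with the same patients.

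Unplanned ICU admission and length of stay are both named secondary clinical outcomes. If the claim stands, a null ICU result will be read as coming from a comparison with 80% power to find a 0.3-point difference, when the audit cohort has almost no ability to detect it.

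**Working it through.** **Inputs.** From the Sample size section: 270 records per time point per arm, two time points pooled, design effect 1.5, and the rates and medians quoted above. From Data analysis: 5% significance, taken as two-sided, and the median test. Allocation is 1:1. Pooling gives 2 × 270 = 540 per arm. The article does not print 540; it is derived, and it counts vital-sign records, so the number of patients behind it is lower if patients contribute repeated records.

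**Formula for two proportions.** With p̄ the mean of p1 and p2,

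n per arm = [z(1−α/2)·√(2p̄(1−p̄)) + z(power)·√(p1(1−p1) + p2(1−p2))]² / (p1 − p2)²

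**Step 1: the plan's own figures that reproduce.**
- Primary, 50 vs 70%, two-sided 1%, 90% power: n = 177; 177 × 1.5 = 265.5, against 270 stated.
- MET calls and mortality/code blue, 3 vs 0.7%, two-sided 5%, 80% power: n = 538. At 540 per arm, power is 80.2%.

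The second match indicates that 540 per arm, with no design effect, was the basis for the 3 vs 0.7% figures.

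**Step 2: ICU admission, 1.2 vs 0.9%.**
- Required n at two-sided 5%, 80% power: 18,121 per arm. With the design effect: 18,121 × 1.5 ≈ 27,200.
- Variants: 18,782 with continuity correction, 14,274 one-sided, 26,964 at two-sided 1%.
- Power at 540 per arm: 7.0% (12.3% one-sided).
- Expected events at 540: 540 × 0.012 = 6.5 against 540 × 0.009 = 4.9, under two events apart. Even a fall from 1.2% to zero would have only 72% power.

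**Step 3: could the audit yield enough patients?** Eight to ten wards in each of four hospitals gives 16 to 20 wards per arm. There are three audit days at each of two post-intervention time points, so six days. Eighteen beds is the eligibility floor; 30 beds, full occupancy and complete patient turnover between audit days are my assumptions, and every bed is counted whether or not the patient has abnormal signs.
- Ceiling: 16 × 18 × 6 = 1,728 to 20 × 30 × 6 = 3,600 per arm.
- ICU power before any design effect: 13.7% at 1,728 and 23.8% at 3,600.
- With 18 wards per arm, 18,121 would require 18,121 / (18 × 6) ≈ 168 different patients per ward per audit day.

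**Step 4: length of stay, 12 vs 10.4 days, IQR 20.**
- Normal shape: SD = 20/1.349 = 14.83. For means, n = 2(1.960 + 0.842)² × 14.83² / 1.6² = 1,348 per arm. The median test multiplies this by π/2, giving 2,117. With the design effect these become 2,022 and 3,176.
- Lognormal shape with median 12 and IQR 20: σ = 1.125 and log(12/10.4) = 0.143, so n = 970 on the log scale or about 1,523 for a median test.
- Power at 540, normal shape: 43% for means, 29% for the median test.
- Detectable difference at 540 with 80% power, before any design effect: 2.5 days (means) or 3.2 days (median test) under the normal shape; 2.1 or 2.6 days under the lognormal. The stated figure is 1.6.

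**Step 5: length of stay at a larger yield.** At 18 × 30 × 6 = 3,240 per arm, the median test under the normal shape has 93% power, or 81% with the design effect of 1.5. At 1,728 or more per arm, however, power for 3 vs 0.7% exceeds 99%, so 2.3 points would no longer be the minimum detectable MET difference.

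**The case against.** The strongest reply concerns the denominator. The 270 is a required minimum for the primary outcome, counted in vital-sign records, and no patient number is stated for ICU admission or length of stay. The section is not uniform either: its adherence odds ratio of 1.8 (50 vs 64.3%) reproduces approximately at 270/1.5 = 180, with 78% power at 5%, so with the design effect, whereas 3 vs 0.7% reproduces only without it. Two matches at 540 therefore do not prove that ICU and length of stay were computed at 540. This stands, and it is why the denominator has to be stated. It does not rescue the ICU figure, which fails at every size the audit could plausibly reach.

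A reader might infer that the length-of-stay claim is equally out of reach. The documents do not support that: Step 5 shows that a large audit yield could deliver it, even after the design effect.

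Table 1 also lists hospital clinical databases as a source for patient outcomes including ICU admission and length of stay. The article gives no counts from them, and the Sample size section ties its figures to the two pooled time points, so a database denominator can be neither confirmed nor computed.

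A reader might also infer that the health-economic comparison is underpowered for the same reason. That does not follow. Under Cost analysis, cost, length of stay and ICU length of stay are analysed on all study-ward admissions over six months against the preceding six months, and the audit-cohort power statement does not govern that analysis.

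Finally, these are secondary outcomes and the primary calculation reproduces. That is correct, and it limits the consequence.

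**Conclusion.** The ICU power statement is wrong for the audit cohort. It needs about 18,100 patients per arm before clustering and about 27,200 after. Power is about 7% at the implied 540 and about 14 to 24% at an assumed ceiling of 1,700 to 3,600. No choice of sidedness, continuity correction or significance level (5% or 1%) that was tried closes the gap. A 0.3-point ICU difference and a 2.3-point MET difference cannot both be minimum detectable differences at one sample size.

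The length-of-stay statement is less certain. It does not reproduce at 540, where the detectable difference is about 2.1 to 3.2 days depending on test and distribution. It could hold at a much larger yield, but then the MET figure would not be a minimum. The four figures therefore cannot share one denominator.

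These conclusions rest on two-sided 5% tests, on 540 as a derived minimum in records rather than a planned patient count, and, for the ceiling, on the assumed bed numbers, occupancy and turnover. The primary sample size and the cost analysis are not affected.

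**What to change.** In the Sample size section:

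1. State the patient denominator, the significance level and whether the design effect was applied for each secondary power figure.
2. Recompute the detectable differences for unplanned ICU admission and length of stay at the expected number of patients, with the clustering allowance and, for length of stay, for the planned median test.
3. Withdraw the claim of 80% power for ICU admission at 1.2 vs 0.9% in the audit cohort, and report that outcome there as an estimate with a confidence interval.

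If another data source was meant for ICU admission, name it and show its count. The cost is less favourable stated figures. No extra patients are needed, and randomisation and the primary analysis are unchanged.
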